# Cognitive bias modification Utilised to Rectify Errors for Depression (CURED): a double-blind, parallel-group feasibility randomised controlled trial in adults with depression

**DOI:** 10.1186/s13063-026-09668-6

**Published:** 2026-04-06

**Keywords:** Depression, Anxiety, Cognitive bias modification for interpretation, CBM-I, Interpretation bias modification, CBM-errors, Randomised controlled trial, Feasibility trial, Digital mental health intervention, mHealth

## Abstract

**Background:**

Depression is a leading cause of global disability, yet access to evidence-based treatments such as CBT remains limited due to shortages of trained clinicians. Scalable, low-cost interventions offer a potential solution. Cognitive Bias Modification for Interpretation (CBM-I) is a promising candidate that is grounded in cognitive theory and backed by evidence. However, effects in depression have been weaker. To address previous limitations, we recently developed CURED (Cognitive bias modification Utilised to Rectify Errors for Depression), a six-session intervention co-developed with individuals with lived experience of depression and refined with clinician input. This study aims to evaluate the feasibility, acceptability and safety of CURED.

**Methods:**

This study is a double-blind, parallel-group feasibility randomised controlled trial recruiting 60 adults meeting inclusion criteria for clinical depression. Participants are allocated 1:1 either to the CURED intervention or a neutral CBM-I control matched for format, length, and delivery, though differing in content. Both arms involve six weekly sessions delivered via mailed pen-and-paper booklets, with remote researcher support to ensure fidelity, and assessment at baseline, post-treatment (6 weeks) and 12-week follow-up. Primary outcomes are feasibility (response, recruitment, eligibility, randomisation, retention, weekly assessment completion, adherence, and randomisation rates); acceptability (Credibility and Expectancy Questionnaire, Exit Questionnaire, and qualitative interviews); integrity of blinding; and safety (adverse and serious adverse events). Secondary outcomes include interpretation bias, depressive and anxiety symptoms, cognitive content and processes, and psychosocial functioning. Analyses will summarise feasibility metrics descriptively and provide variance estimates to inform sample size calculations and primary outcome selection for a future definitive trial.

**Discussion:**

CURED has the potential to address the pressing need for accessible, evidence-based interventions for depression. This feasibility trial will establish whether CURED is feasible, acceptable, and safe. If successful, a fully powered, definitive efficacy randomised controlled trial will be warranted.

**Trial registration:**

ISRCTN51689816, https://www.isrctn.com/ISRCTN51689816. Prospectively registered on 16 June 2025. Recruitment started on 16 July 2025 and is anticipated to be completed by 1 July 2026.

## Introduction

### Background and rationale {9a}

Depression stands out as one of the leading causes of global disability regardless of decades of intervention efforts [1], with a steadily increasing prevalence over the past three decades [2]. Although evidence-based approaches such as cognitive-behavioural therapy (CBT) are endorsed as gold-standard treatments by the National Institute for Health and Care Excellence (NICE) and the National Institute of Mental Health (NIMH), many individuals remain unable to access these treatments [3]. The main barrier appears to lie in the shortage of adequately trained clinicians [3]. This highlights the pressing need for scalable, accessible interventions.

Cognitive bias modification for interpretation (CBM-I), rooted in cognitive theory [4, 5] and supported by an expanding body of evidence [6, 7], emerges as a promising candidate. CBM-I is designed to shift the interpretation of emotionally ambiguous stimuli away from negative meaning and toward benign or positive interpretations [8]; see Fig. 1 for an example CBM-I item. The central role of interpretation bias (i.e. the mechanism targeted by CBM-I) has been consistently demonstrated in depression by meta-analyses on cross-sectional [9], longitudinal [10], and experimental studies modifying interpretation bias to reduce depressive symptoms [6]. Despite these findings, CBM-I appears to perform worse for depression compared to anxiety [6].

**Fig. 1 Fig1:**
[figure not shown]
An example CURED item

CBM-I was originally designed for anxiety; typical therapeutic content reflects core fears and processes specific to anxiety rather than depression [11]. Cognitive bias modification for cognitive errors (CBM-errors) was developed to rectify cognitive distortions in line with the cognitive thinking patterns (so called “errors”) originally identified and defined in Beck’s cognitive theory of depression [4, 12]. As well as targeting the full spectrum of depressive cognitions, training items are derived directly from clinical practice to provide maximum depression relevance [11, 12]. Early studies yielded encouraging preliminary findings [11], yet gains did not reliably extend to symptom improvement, underscoring the need to overcome existing limitations to achieve full therapeutic impact.

Insufficient number of sessions (i.e. one to two sessions) and disorder-specificity of the content stand out as the main limitations of CBM-Errors [12]. Indeed, the wider evidence base suggests that higher effect sizes can be obtained when a larger number of sessions [13] and disorder-specific therapeutic content is used [14, 15].

To address these limitations, we extended CBM-errors into a six-session intervention called CURED (cognitive bias modification utilised to rectify errors for depression) by generating new content co-created with people with lived experience of depression. New materials were evaluated by lived-experience experts and clinicians specialising in depression ([name], [name], [name], [name], [name], [name], et al: Beyond CBM-errors: the material development and evaluation of CURED (Cognitive bias modification Utilised to Rectify Error for Depression), In preparation). Evidence regarding feasibility, acceptability, and variance estimates is now needed to further CURED’s clinical translation pathway. This paper reports the protocol for a double-blind, parallel-group feasibility randomised controlled trial that aims to evaluate the feasibility, acceptability and safety of CURED.

### Explanation for the choice of comparator {9b}

We will employ a well-established control condition, validated in multiple prior CBM-I studies [16, 17]. This condition matches the intervention in all procedural features, delivery format, number and length of scenarios, structural format, and imagery instructions, with the sole difference being that the content focuses on emotionally neutral, everyday activities and factual descriptions. By holding other factors constant such as reading time, sentence length, delivery modality, guided imagery, and the word-completion task, this design isolates rectifying cognitive errors as the critical experimental variable.

### Objectives {10}

The specific objectives are to provide the following:

Feasibility metricsAcceptability metricsSafety assessmentAssessment of candidate outcome measuresProviding descriptive data and variance estimates for future trials

## Methods: patient and public involvement, and trial design

### Patient and public involvement {11}

Intervention materials were co-developed with patient and clinician involvement. Ten members of Maudsley Biomedical Research Centre’s Service Users Advisory Group (SUAG) generated 200 ambiguous daily-life scenarios across seven domains (e.g. work, study, relationships, leisure, health, and social interactions), following written guidance on cognitive bias modification and key cognitive error types including overgeneralisation, personalisation, catastrophising, dichotomous (“all-or-nothing”) thinking, and discounting the positive. The research team refined these into 181 standardised items, each comprising three lines of ambiguous text, a positive resolution (final word with missing vowels), a title, and a comprehension question. These newly developed items were added to previous CBM-Error content to create a total set of 282 intervention items. Control items (*n* = 240) were adapted from previous work on the STOP intervention, as the same neutral scenarios can serve as control materials across CBM-I paradigms [17]. All items were evaluated for readability by eight individuals with lived experience of depression and for negativity by eight clinicians with 6 months of therapeutic experience in depression. Finally, lived-experience co-author SM, the FAST-R panel, and King’s YPMHAG reviewed the protocol and participant-facing documents.

### Trial design {12}

Participants (Table 1) will be randomised to CURED or the placebo control procedures with assessments carried out at baseline (pre-randomisation); 6 weeks (immediately post-intervention); and 12-week follow-up. Primary outcomes will be collected at baseline, post-intervention, and 12-week follow-up, while a subset of measures will be administered after each weekly session throughout the 6 weeks of the intervention. A detailed overview of study procedures is provided in the CONSORT flow diagram (Fig. 3) and SPIRIT participant timetable (Table 2).

**Table 1 Tab1:** Characteristics for the population planned to be sampled

**Characteristic**	**The people we would expect to see included**
Age	Anyone aged 18 or above
Sex	Sex at birth information is collected for randomisation purposes (see {*21b*} for details)
Gender	All are included. Male, female, non-binary, prefer not to say, and other (please specify) options are available for participants to select
Race, ethnicity and ancestry	The study uses the UK Census standard framework for data collection regarding race, ethnicity, and ancestry. There are no inclusion or exclusion criteria related to race, ethnicity, and ancestry
Socioeconomic status	Socioeconomic status is assessed using two items from the demographic questionnaire: 1. Highest level of education completed: No formal education/primary education/secondary education/associate degree/bachelor’s degree/master’s degree/doctorate/other (specify) 2. Annual household income: Less than £20,000/£20,000–£39,999/£40,000–£59,999/£60,000–£79,999/£80,000–£99,999/£100,000 or more There are no inclusion or exclusion criteria related to socioeconomic status
Geographic location	IoPPN, King’s College London (London, UK), however no in-person attendance is needed to participate. Any participant resident in England or Wales can participate. Participants must have access to an internet connection to complete the study procedures remotely
Other characteristics relevant to the trial	Mild self-reported depression or above determined by scoring above threshold on the Beck Depression Inventory-II (≥ 15) and answering “yes” to either or both of two MINI Screen depression questions

**Table 2 Tab2:** The SPIRIT participant timeline of the CURED feasibility trial

	**Screening (-T**_**1**_** to T**_**0**_**)**	**Baseline (T**_**0**_**)**	**Interim assessments (T**_**i1-5)**_^**c**^	**6-week follow-up assessment **(**T**_**1**_**)**	**12-week follow-up (T**_**2**_**)**
Enrolment					
* Informed consent procedures*					
Participant information sheet	X				
Consent form	X				
*Eligibility check*					
Inclusion/exclusion criteria checklist	X				
Capacity assessment tool (if applicable)	X				
M.I.N.I. screening tool	X				
Beck depression inventory–II (BDI-II)	X	X		X	X
Intervention/comparator					
CURED (intervention)					
Neutral CBM-I (control)					
Assessment instruments					
*Sociodemographic information*					
Socio-demographic questionnaire		X			
*Clinical symptoms*					
M.I.N.I. MDD module		X			
Patient Health Questionnaire-9 (PHQ-9)		X	X	X	X
Beck Depression Inventory-II (BDI-II)		X		X	X
Depression, Anxiety, and Stress Scale-21 (DASS-21)		X		X	X
Generalized Anxiety Disorder-7 (GAD-7)				X	X
*Interpretation bias*					
Scrambled Sentence Task (SST)		X C/bal^b^	X C/bal	X C/bal	X C/bal
Similarity Rating Test (SRT)		X C/bal		X C/bal	X C/bal
*Cognitive content*					
Automatic Thought Questionnaire-Revised (ATQ-R)		X		X	X
Cognitive Distortions Scale (CDS)		X		X	X
*Prospective Imagery Task (PIT)*		X		X	X
*Cognitive process*					
Repetitive Thinking Questionnaire (RTQ-10)		X		X	X
Interpretation Inflexibility Task (IIT)		X		X	

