***Psychosocial functioning and mood***					
Recovery of Quality of Life-20 (ReQoL-20)		X		X	X
Visual Analogue Scale (VAS) for mood (happy, sad, anxious)			X		
Global rating of change (GRC): 1 item				X	

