#### Secondary outcomes

The secondary outcomes will assess the suitability of candidate clinical and cognitive measures as potential primary outcomes in a future definitive RCT. This includes evaluating their sensitivity to change over time and estimating between-group effect sizes (with 95% confidence intervals) to inform sample size calculations (please see Table 2 for the full assessment schedule).

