**Generalised Anxiety Disorder-7 (GAD-7 **[28]**)**

A 7-item self-report questionnaire evaluating anxiety severity on a 0–3 scale, with higher scores reflecting greater anxiety.

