### Harms {17}

The intervention paradigm, cognitive bias modification for interpretation (CBM-I), has been evaluated in over 100 trials and has consistently been found to be safe and no riskier than standard care [7]. The primary potential harm is temporary distress during task completion for the intervention group when reading content which could trigger depressive thoughts. Prior feasibility data on the predecessor of CURED, CBM-Errors, indicated that participants’ immediate mood was typically unaffected or slightly improved following sessions [12]. Adverse Events (AEs) information will be proactively collected at the 3-week check-in call using an adapted version of the Adverse Events Checklist, and an exit interview will provide a further opportunity for adverse event data gathering. If a participant experiences persistent mood deterioration, distress impairing daily functioning, or any indication of risk to self or others, participation will be paused, a risk assessment made and, if appropriate, clinical care will be arranged (e.g. referral to the participant’s GP or mental health team). All AEs judged to be serious, according to the standard HRA definition, will be reported to the Sponsor and REC in line with governance requirements. All adverse events will be presented descriptively by frequency, relatedness to the intervention, severity and seriousness to provide comprehensive safety data which will be reported in trial outputs.

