### Secondary outcomes

Secondary outcomes will be assessed as candidate primary outcomes and used in providing effect size estimates for power calculations for future trials.Suitability of the candidate primary outcomes will be defined by:Acceptability (feedback on burden and clarity from exit questionnaires),Variability (sufficient spread in scores without floor/ceiling effects),Sensitivity to change, defined as evidence of within-group and between-group score changes over time in the expected direction (mean change scores with 95% CIs).Descriptive statistics will be aggregated by assigned condition and presented in tables, including means, medians, standard deviations, variances, range, 95% confidence intervals and levels of missingness.

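### Table 2 schedules GAD-7 only at 6 and 12 weeks, although its suitability as a candidate primary outcome is to be judged partly on change scores

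*Protocol article*

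**What the plan says.** The Outcomes {16} section lists the GAD-7 among the secondary clinical symptom measures: "A 7-item self-report questionnaire evaluating anxiety severity on a 0–3 scale, with higher scores reflecting greater anxiety". It gives the purpose of the secondary outcomes as "evaluating their sensitivity to change over time and estimating between-group effect sizes (with 95% confidence intervals) to inform sample size calculations", and refers the reader to Table 2 for the full schedule.

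The secondary-outcome part of the statistical methods {27a} says: "Secondary outcomes will be assessed as candidate primary outcomes and used in providing effect size estimates for power calculations for future trials". Suitability has three parts: acceptability, variability and sensitivity to change. The third is defined as evidence of "within-group and between-group score changes over time in the expected direction (mean change scores with 95% CIs".

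In Table 2 (Trial design {12}) the row "Generalized Anxiety Disorder-7 (GAD-7" has marks at T1 (6 weeks) and T2 (12 weeks) and none at screening, baseline or the interim points. The row directly above, "Depression, Anxiety, and Stress Scale-21 (DASS-21", is marked at baseline, T1 and T2.

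The Data management {26} section says in general terms that questionnaires are given at baseline, post-treatment and 12 weeks. It does not name the GAD-7.

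**The concern.** The schedule and the suitability criterion do not fit together. A change score across treatment needs a value from before treatment, and the printed schedule provides none for this scale. Trial design {12} places the baseline assessment before randomisation, so T1 is the first GAD-7 value and it comes after the six sessions.

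The trial is meant to supply variance estimates and effect sizes for a definitive trial. For the GAD-7 it could not supply the SD of change or the correlation between baseline and follow-up, which are the quantities needed to size a trial analysed by change scores or with baseline adjustment. The anxiety candidates would also be compared on unequal evidence: DASS-21 anxiety could be tested against the change criterion, and the GAD-7 could not.

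The gap is not a matter for a later analysis plan. The section on the protocol and statistical analysis plan {5} says that the plan is contained in {27a–d}, and no analysis recovers a value that was not collected.

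**Working it through.** **Schedule, row by row (Table 2).**

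| Secondary measure | Baseline | Interim | T1 | T2 |
|---|---|---|---|---|
| PHQ-9 | yes | yes | yes | yes |
| BDI-II | yes | no | yes | yes |
| DASS-21 | yes | no | yes | yes |
| GAD-7 | **no** | no | yes | yes |
| SST | yes | yes | yes | yes |
| SRT | yes | no | yes | yes |

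The neighbouring rows fill the same columns, so a shifted column does not explain the gap. The remaining secondary measure, the M.I.N.I. MDD module, is a baseline diagnostic interview and is not repeated. The GAD-7 is therefore the only repeated secondary measure without a baseline mark.

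**Count.** Sample size {19} gives 30 per arm, 2 × 30 = 60. Participants with a computable change from baseline to T1 or T2 on the GAD-7 under Table 2: 0 of 60. The only available change is T1 to T2, which begins after treatment has ended.

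**Precision.** The article gives no correlation r between baseline and follow-up, so r = 0.5 to 0.7 is assumed, with equal SDs at both times and complete data.

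- Unadjusted post-scores: 95% CI half-width = t(0.975; 58) × √(2/30) = 0.52 SD.
- Change scores (the statistic named in {27a}): SD of change = √(2(1 − r)) × SD. At r = 0.5 the factor is 1.00, so the half-width is 0.52 SD. At r = 0.7 the factor is √0.6 = 0.775, so it is 0.517 × 0.775 = 0.40 SD.
- Baseline-adjusted (ANCOVA): factor √(1 − r²). At r = 0.5 the half-width is 0.45 SD; at r = 0.7 it is 0.37 SD.

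Width of the post-score interval relative to each alternative:

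| r (assumed) | against change score | against ANCOVA |
|---|---|---|
| 0.5 | 1/1.00 = 1.00 (0% wider) | 1/√0.75 = 1.155 (15% wider) |
| 0.7 | 1/0.775 = 1.29 (29% wider) | 1/√0.51 = 1.40 (40% wider) |

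The first column corresponds to the stated analysis. The second applies only if a baseline-adjusted analysis is used, which the article does not state.

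**How many participants a change could still reach.** The first randomisation was on 18/08/2025 (Trial status) and the article was published on 2026-04-06, which is 231 days or about 7.6 months. At the target of five per month, assumed met, 7.6 × 5 = 38 would have been randomised, leaving 22 of 60, or roughly a third.

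**The case against.** The strongest reply is that the GAD-7 may well be taken at baseline and that a mark was lost from the table. Every other repeated secondary measure has one, and both Trial design {12} and Data management {26} speak of baseline assessment in general. This stands as a live explanation, so the documents do not support a flat statement that the GAD-7 is not measured at baseline. They do show that Table 2, which the outcomes section names as the full schedule, conflicts with {27a}.

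Secondly, much can be done without a baseline. Randomisation keeps the post-score contrast unbiased, an effect size with its interval can be estimated from it, and acceptability and variability can be judged as planned. This also stands. A reader might infer that chance imbalance between the arms (SD √(2/30) = 0.26 SD units) could not be corrected at all. That goes too far: baseline DASS-21, PHQ-9 or BDI-II can serve as covariates, and the unadjusted interval already includes this chance variation. Only adjustment for the GAD-7 itself is lost.

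A reader might also extend the point to the mood scales, "Visual Analogue Scale (VAS) for mood (happy, sad, anxious", which are marked only at the interim points, after each session, while Harms {17} says "The primary potential harm is temporary distress during task completion for the intervention group". The documents do not support calling this an error. The scales are exploratory, no change from before to after a session is promised, and post-session mood can be compared with the randomised control arm. An immediate within-person session effect cannot be estimated, but the plan does not claim to estimate one.

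**Conclusion.** The point holds for the GAD-7 as an inconsistency between the schedule and the suitability criterion. As printed, change across treatment is available for 0 of 60 participants, and the sensitivity-to-change criterion cannot be applied over the treatment period to one of the candidate outcomes. The loss of precision for the between-arm contrast is 0–29% in interval width against the stated change-score analysis and 15–40% against ANCOVA, both resting on the assumed correlations of 0.5 to 0.7.

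The weight is moderate: it should be fixed. The trial is descriptive, has no single primary clinical endpoint, keeps three depression scales with baselines, and retains an anxiety change measure in the DASS-21. The sample size is unaffected.

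**What to change.** First establish what is being done. If the GAD-7 is already collected at baseline, correct Table 2; nothing else is needed.

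If it is not collected:

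- Add the GAD-7 to the online baseline assessment for participants still to be enrolled.
- For those already randomised, report GAD-7 post-scores by arm, optionally adjusted for baseline DASS-21 anxiety.
- State in {27a} that the DASS-21 anxiety subscale is the anxiety candidate assessed against the change criterion, and that the GAD-7 is assessed on acceptability, variability and post-scores.

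The cost is seven items, about 2 minutes at baseline, and a schedule amendment. The drawback is that baseline GAD-7 would exist for only part of the sample: roughly a third if the change had been made when the article was published and the recruitment target was met, and fewer the later it is made. Any GAD-7 change scores from that subset should be reported with their own denominator.
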